## Abstract

**Background:**

Patients receiving surgical treatment of acute type A Aortic Dissection (aTAAD) are common to suffer organ dysfunction in the intensive care unit due to overwhelming inflammation. Previous studies have revealed that glucocorticoids may reduce complications in certain patient groups, but evidence between postoperative glucocorticoids administration and improvement in organ dysfunction after aTAAD surgery are lacking.

**Methods:**

This study will be an investigator-initiated, prospective, single-blind, randomized, single-center study. Subjects with confirmed diagnosis of aTAAD undergoing surgical treatment will be enrolled and 1:1 randomly assigned to receive either glucocorticoids or normal treatment. All patients in the glucocorticoids group will be given methylprednisolone intravenously for 3 days after enrollment. The primary endpoint will be the amplitude of variation of Sequential Organ Failure Assessment score on post-operative day 4 compared to baseline.

**Discussion:**

The trial will explore the rationale for postoperative application of glucocorticoids in patients after aTAAD surgery.

**Trial registration:**

This study has been registered on ClinicalTrials.gov (NCT04734418).

## Introduction

Acute type A aortic dissection (aTAAD) is a condition featuring high mortality, and surgery is the most common treatment. However, postoperative complications, such as multiple organ failure occur frequently and the prognosis remains to be improved [1].

One of the proposed mechanisms of postoperative complications is the disruption of immune homeostasis throughout the perioperative period. Surgical procedures may serve as a potential trigger for systemic inflammation [2]. Clinically, the occurrence of systemic inflammatory response syndrome (SIRS), which is believed to result in capillary leakage and other major postoperative complications, including ventricular dysfunction, respiratory failure, renal, hepatic and neurological dysfunction, bleeding, and ultimately, multiple organ failure [3], in the early postoperative period significantly increases the incidence of major adverse outcomes and mortality in patients with aTAAD [3, 4]. Inflammatory markers, such as interleukin(IL)-6, are good predictors of postoperative mortality [5]. Moreover, vascular paralysis induced distributive shock after major cardiovascular surgery is also associated with high mortality. At the core of its cause may be the activation of the inflammatory cascade with increased circulating levels of IL-1, IL-6, and tumor necrosis factor-α [6].

To alleviate the negative impacts of inflammatory response in the perioperative period of cardiac surgery, there have been successive studies reporting the effects of glucocorticoid (GC) administration in recent years. For instance, Dexamethasone for Cardiac Surgery (DECS) and Steroids in Cardiac Surgery trials have analyzed major clinical outcomes such as mortality after administrating GC during cardiac surgery [7, 8]. In addition, Halonen et al. revealed that the occurrence of postoperative atrial fibrillation was significantly lower after hydrocortisone administration as atrial fibrillation is believed to be bound up with postoperative inflammation [9, 10]. With regarding to vascular paralysis induced hypotension, recent clinical studies such as the APROCCHSS trial, have noted that the use of low doses of GC improves 90-day mortality and increases the likelihood of shock reversal in intractable shock [11].

However, numerous investigators have pointed out the use of GC in cardiac surgery remains controversial. Not only whether GC would lead to mortality benefits, but also how GC should be used are still inconclusive. Although meta-analysis has not revealed mortality benefits, certain patient groups may still benefit from GC [12]. More importantly, in previous clinical trials, GC was used prophylactically with a bolus style regimen, without sufficient tapering. Such a regimen may achieve inflammatory regulation at the expense of hypothalamic–pituitary–adrenal axis suppression.

The aim of this trial is to investigate whether postoperative GC, with a tapering regimen, would improve prognosis in patients with aTAAD undergoing surgery.

## Materials and methods

### Setting

This study will be an investigator-initiated, prospective, single-blind, randomized, single-center study, which will investigate the effect of postoperative GC on patients with aTAAD. The trial will be conducted in the cardiac intensive care center of Zhongshan Hospital, Fudan University.

### Overview

All patients with aTAAD undergoing surgery will be screened for study eligibility. Upon enrollment, eligible patients will be randomized 1:1 to one of the two treatment arms (i.e. GC or normal treatment) (Fig. 1). Data will be collected until hospital discharge or death.

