**Fig. 2 Fig2:**
[figure not shown]
Diagram of interventions

The first dose of MP will be given on the morning of postoperative day (POD) 1 at a dosage of 2 mg/kg/d, followed by another dose with the same dosage 12 h later. On POD 2 and POD 3, MP will be reduced to 1 mg/kg/d and 0.5 mg/kg/d respectively, with 12 h intervals between two injections.

All patients in the control group will receive treatments as usual without the administration of GC. Patients will be required to be supervised by medical personnel when administering the study drug, and their vital signs will be checked regularly in case of emergency.

Strategies to improve adherence to intervention and monitor adherence to procedures will be implemented. Three dedicated research fellows will screen all patients who enter the ICU after surgery. They will be responsible to check if certain candidate meets the study criteria. They will also be in charge of ensuring that intervention will be prescribed based on the protocol. In addition, two independent intensive care specialists will monitor adherence to interventions throughout the study period.

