### Outcomes

The primary outcome will be the difference of Sequential Organ Failure Assessment (SOFA) score on POD 4 compared to baseline (on POD1 before MP administration).

Secondary outcomes will be in-hospital mortality, days of ICU stay; days of hospital stay; duration of mechanical ventilation; tracheotomy; continuous renal replacement therapy; postoperative infection; inflammatory markers on POD 1, 2 and 3; composite endpoint (in-hospital morbidity and mortality or ICU stay over 30 days or tracheotomy).

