### ***Data to be collected*** (Table 1)

**Table 1 Tab1:** Data to be collected

Time Points	Day of ICU admission	Treatment					
		Preoperative	Pre-drug	24 h	48 h	72 h	Discharge or death
Enrollment	x						
Informed consent	x						
Inclusion and exclusion criteria	x						
Demographics^a^	x						
Past medical history^b^	x						
Pre-operative cardiac function^c^	x						
Operative information^d^	x						
Assessment							
Temperature		x	x	x	x	x	
Respiratory rate		x	x	x	x	x	
Heart rate		x	x	x	x	x	
Systolic blood pressure		x	x	x	x	x	
Diastolic blood pressure		x	x	x	x	x	
SOFA score	x			x	x	x	
Methylprednisolone administration				x	x	x	
Inflammatory indicators^e^		x	x	x	x	x	
Blood count^f^		x	x	x	x	x	
Blood biochemistry^g^		x	x	x	x	x	
Arterial blood gas^h^		x	x	x	x	x	
Concomitant medications^i^		x	x	x	x	x	
Adverse events^j^				x	x	x	x
24 h fluid intake and output		x	x	x	x	x	

*TIA* Transient ischemic attack, *COPD* Chronic obstructive pulmonary disease, *DM* Diabetes mellitus, *NYHA* New York Heart Association, *LVEF* Left ventricular ejection fractions, *TAPSE* Tricuspid annular plane systolic excusion, *ECG* Electrocardiogram, *ALICE* Albumin-indocyanine green evaluation, *ICU* Intensive care unit, *CCB* Calcium channel blockers, *CRP* C-reactive protein, *PCT* Procalcitonin, *ESR* Erythrocyte sedimentation rate, *TNFα* Tumor necrosis factor-α, *IL-6* Interleukin-6, *IL-10* Interleukin-10, *pH* potential of Hydrogen, *CRRT* Continuous renal replacement therapy

^a^age, sex, height(cm), weight(kg), smoking and alcohol consumption

^b^pre-existing definite preoperative diagnosis; previous or screening period medical history (including at least hypertension, TIA, COPD, stroke, DM, various arrhythmias, peptic ulcer)

^c^preoperative NYHA classification, preoperative cardiac ultrasound including LVEF, TAPSE, preoperative ECG, myocardial enzyme profile, preoperative ALICE score for entrapment

^d^name of the procedure, duration of the procedure (min), time outside the body (min), time of block (min), time of transfer to the ICU. Intraoperative dose and time of hormone use, blood loss, and transfusion volume; β-blockers, CCB, anticoagulants such as aspirin, antiplatelet agents, antihypertensive agents, cardiotonic agents, proton pump inhibitors or H2-blockers, antibiotics used within the previous 7 days

^e^CRP, PCT, ESR, TNFα, IL-6, IL-10

^f^hemoglobin, white blood cell, neutrophil count, lymphocyte count, platelet count

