### Data collection and storage

Blinded trial investigators will enter the baseline characteristics, process variables, and outcome data from the patient files into web-based case report forms (Electronic Data Capture System) from POD 1 to POD 4, and follow up at discharge from hospital. Calculation of the SOFA score will be done by the on-duty physician. Personal information about potential and enrolled participants will be collected and maintained. The initial of patient’s full name will be used instead of the real name to identify certain patients. In addition, during the study period, a unique identification number will be used as the dominant way to follow certain patients to protect confidentiality. If necessary, information stored in the electronic patient record will be used for follow-up and patients or their surrogates will be contacted directly if additional data is needed. Data will be stored in a third-party system and the trial investigators have full access to it.

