### Subgroup analyses

The effect of the treatment among different subgroups: (1) gender, (2) diabetes, (3) The European System for Cardiac Operative Risk Evaluation (EuroSCORE) II, (4) Cardiopulmonary Bypass (CPB) duration, (5) age, (6) high sensitivity C-reactive protein on POD 1 and (7) SOFA on POD 1 will be analyzed. Stratified analysis using a logistic regression or Cox proportional hazards model, as applicable, will be performed. By adding a product term to the model that already contains the treatment and the subgroup factor, the interaction between each subgroup factor and the treatment group will be tested.

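### As written, patients are randomised before the POD 1 baseline SOFA is taken, Table 1 disagrees on when that score is recorded, and nothing fixes it before allocation is released

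*Protocol article*

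**What the plan says.** - **Randomisation.** Overview: "Upon enrollment, eligible patients will be randomized 1:1 to one of the two treatment arms". No clock time is given for randomisation or for release of the allocation.
- **Enrolment.** In Table 1 the rows for enrolment, consent and eligibility are marked only in the column "Day of ICU admission".
- **Primary baseline.** Outcomes: SOFA on POD 4 is "compared to baseline (on POD1 before MP administration").
- **First dose.** Intervention: "The first dose of MP will be given on the morning of postoperative day (POD) 1".
- **Control arm.** Intervention: "All patients in the control group will receive treatments as usual without the administration of GC". No placebo is described.
- **SOFA schedule.** Table 1 marks SOFA on the day of ICU admission and at 24, 48 and 72 h. The Pre-drug cell of that row is empty, although most other assessments have a mark there.
- **Blinding.** Randomization and blinding: the doctors and nurses giving the drug know the allocation but take no part in assessing outcomes; patients and the researchers who collect and analyse data are blinded.
- **Scorer.** Data collection and storage: "Calculation of the SOFA score will be done by the on-duty physician".
- **Subgroups.** Two of the factors are "high sensitivity C-reactive protein on POD 1 and (7) SOFA on POD 1".

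**The concern.** The primary outcome is a change score, so any between-arm difference in how or when the baseline is obtained passes one-for-one into the estimated treatment effect. Two routes are open.

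The first is knowledge of the arm. If allocation is released at enrolment and the baseline is scored on the POD 1 morning, clinicians in an unmasked trial may know the arm when they score. SOFA can also reflect support decisions taken by unblinded staff, so a blinded scorer alone would not fully protect a baseline taken after allocation.

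The second is timing. Methylprednisolone administration is an event that controls never have, and the text gives no common clock time in its place. SOFA is falling at this stage. A later baseline in one arm would start lower and show less apparent improvement in that arm.

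The contradiction in Table 1 adds to this, because two sites of the document imply two different baseline values for the same endpoint.

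**Working it through.** **Step 1. The order of events, from the text.**

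| Event | Place | Timing |
|---|---|---|
| Enrolment, consent, eligibility | Table 1 | Day of ICU admission |
| Randomisation | Overview | At enrolment |
| Baseline SOFA, version A | Outcomes | POD 1, before the drug |
| Baseline SOFA, version B | Table 1 | Day of ICU admission; Pre-drug empty |
| First dose | Intervention | Morning of POD 1 |

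Under version A the baseline follows randomisation and precedes the drug. Under version B the score shares a column with enrolment, and the document does not say which comes first. Neither version fixes the score before the allocation is released.

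**Step 2. Who scores.** One section keeps unblinded staff out of outcome assessment. Another gives the SOFA calculation to the on-duty physician, without saying that this person is not one of the treating doctors. Blinded investigators enter data from the patient files, but that step comes after the score has been calculated. The two sections can be reconciled only by a statement that the document does not contain.

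**Step 3. Reproduce the plan's own figure.** Inputs from Sample size: decline 2.87, SD 1.69, a 25% larger reduction, two-sided alpha 0.10, power 0.90.

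- Target effect: 0.25 x 2.87 = 0.7175 points.
- n per group = 2 x [1.69 x (1.645 + 1.282) / 0.7175]^2 = 95.02, rounded up to 96; total 192.
- Dropout: 192 x 1.1 = 211.2, rounded up to 212.

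The plan's 96/192/212 is reproduced. The order of randomisation and baseline does not enter this formula, so the sample size is unaffected.

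**Step 4. Scale of a timing difference (assumed).** The decline of 2.87 runs from POD 1 to POD 3, which is two days. If linear, 2.87 / 2 = 1.435 points per day. A 4-hour between-arm difference gives 1.435 x 4/24 = 0.24 points, and 0.24 / 0.7175 is one third of the target effect.

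**Step 5. Sensitivity to a scoring bias (assumed).** With 96 per arm, the standard error is 1.69 x sqrt(2/96) = 0.244. For a bias b and critical value z, the two-sided type I error is 1 - Phi(z - b/SE) + Phi(-z - b/SE).

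| Assumed bias (points) | Share of 0.7175 | Nominal 0.05 becomes | Nominal 0.10 becomes |
|---|---|---|---|
| 0.1 | 14% | 0.07 | 0.13 |
| 0.2 | 28% | 0.13 | 0.21 |
| 0.3 | 42% | 0.23 | 0.34 |

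Both nominal levels are shown because the sample size uses 0.10 and Data analysis uses 0.05. Steps 4 and 5 show sensitivity only. The documents give neither a timing difference nor a bias.

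**The case against.** **The baseline is still before the drug.** A baseline taken after randomisation but before the first dose is common, and the study drug cannot alter it. This stands. It also answers most of the worry about the two POD 1 subgroup factors: hs-CRP is a laboratory value, and Table 1 schedules inflammatory markers before the drug. What remains is scoring or care influenced by a known allocation, which matters more without a placebo.

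**A reader might infer that the scorer already knows the arm, and has known it for hours.** The document does not support that. It bars unblinded staff from outcome assessment, and it gives no time of randomisation, no time of allocation release and no mapping from ICU admission day to POD 1. The Abstract counts the three treatment days from enrolment and the Intervention section counts them from ICU entry, so the interval may be short. The flow chart is not shown.

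**Table 1 may close the gap.** If its admission-day SOFA is the baseline, enrolment and baseline fall on the same day. That is possible, but it contradicts the explicit endpoint definition and still does not put the score ahead of allocation.

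**A reader might infer that the arms are in fact scored at different times.** The text ties the baseline to POD 1 for both arms, and nothing shows a systematic difference or its direction. It is also tempting to say that a 12-hour shift would equal the whole target effect. That is an identity: 25% of a two-day linear fall is half a day's fall. It is not evidence of bias.

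**First-night losses.** Patients re-operated on or withdrawn before the POD 1 morning could be randomised without a baseline. The plan has a 10% dropout allowance, intention-to-treat analysis and multiple imputation, and the documents give no rate from which to claim material dilution.

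**Conclusion.** The point holds as an unprotected sequence, not as demonstrated bias. Read together, the Overview, Table 1 and the Outcomes section place randomisation before the POD 1 baseline. Table 1 and the Outcomes section contradict each other on when that baseline is recorded. The anchor is an event that exists in one arm only, and the blinding of the person who scores SOFA is unresolved.

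The size is unknown. Against a target of 0.72 points, a 4-hour timing difference would be worth about 0.24 points, assuming a linear decline. An assumed scoring bias of 0.2 points would raise a nominal 0.05 error rate to about 0.13. Both depend on inputs that the documents do not supply. The reading of Table 1 rests on its cell positions as they appear in the available text.

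The change is worth making because it removes a route for bias into the primary outcome at almost no cost.

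**What to change.** 1. Keep screening and consent on the ICU admission day. Release the allocation on the morning of POD 1, only after the baseline SOFA and the hs-CRP sample have been recorded in the electronic data capture system and eligibility has been re-confirmed.
2. Define baseline in both arms as that pre-allocation score, in place of wording tied to methylprednisolone.
3. Correct the SOFA row of Table 1 to match the definition.
4. Reconcile Randomization and blinding with Data collection and storage: state whether the SOFA scorer is blinded and is separate from the staff who give the drug. This matters for the POD 4 score as much as for the baseline, and moving randomisation does not settle it.

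**Cost.** Allocation is released some hours later. Patients who die or are re-operated on during the first night will have been consented but not randomised. No patients, visits or tests are added, the treatment schedule is untouched, and 96/192/212 stands.

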**Fig. 1 Fig1:**
[figure not shown]
Flow chart of study protocol. GC:glucocorticoids; ICD: implantable cardioverter defibrillator

### Study population

Inclusion and exclusion criteria are defined for enrolled patients;

#### Inclusion criteria

Patients meeting all of the following criteria:1. Age 18 years old or above;2. Obtain informed consent from the patient's family or legal representative;3. Confirmed diagnosis of acute type A aortic dissection and received surgical treatment.4. Life expectancy > 3 days after surgery.

#### Exclusion criteria

1. Iatrogenic aortic dissection;2. History of bacterial or fungal infections within the past 30 days;3. History of GCs or anti-inflammatory drug use within the previous 14 days;4. Allergy to GCs;5. Pregnancy;6. Cushing's syndrome or Addison's syndrome;7. History of implantable cardioverter defibrillator or permanent pacemaker implantation;8. Patients with malignancies undergoing chemotherapy, immunotherapy or targeted therapy;9. Patients with severe preoperative hepatic insufficiency;10. Patients with severe preoperative renal insufficiency;

#### Criteria for withdrawing from the study

1. Allergy to GC during the study.2. Complications that require surgical treatment.3. Withdrawal of the informed consent.

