#### Outcomes

##### Postoperative infection

Referring to infection after cardiac surgery, including deep incisional surgical site infection occurring at the primary chest incision, deep incisional surgical site infection occurring at a secondary incision site, mediastinitis, infectious myocarditis or pericarditis, endocarditis, cardiac device infection, pneumonia, empyema, Clostridium difficile colitis, and bloodstream infection, with or without support of pathogenic evidence [16].

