### Data analysis

This study will summarize patient disposition, demographic and other baseline characteristics, study drug exposure, safety and efficacy. Statistical analyses will be performed using R, version 3.5.0 (R Foundation for Statistical Computing, Vienna, Austria). Continuous variables will be summarized descriptively based on mean (Mean), standard deviation (SD), median (Median) and maximum (Max) and minimum (Min) values, and comparisons of differences between groups will be based on whether the data meet a normal distribution with a two independent samples t-test or wilcoxon nonparametric test. The categorical variables will be summarized descriptively based on the number of subjects in each category and their corresponding percentage share using the chi-square test, and the Fisher's exact test will be used to analyze the differences between groups if necessary. Kaplan–Meier curves and log-rank test will be used to estimate hospital survival in patients in both arms.

In addition, intention to treat analyses which will include all participants randomly assigned to the study arms regardless of their loss to follow-up or compliance will be implemented. Per-protocol analyses, which include all participants with complete data sets, will also be performed for primary and secondary outcomes. In case of missing data, multiple imputation will be calculated.

An interim analysis will be conducted when the set reaches 50% of the proposed number of patients; if the primary endpoint has been reached and differences exist, the data safety monitoring board will discuss and vote on whether to allow early termination of the study. Unless otherwise specified, α = 0.05 (two-sided test) and *p* < 0.05 was defined as statistically significant.

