## Discussion

In this prospective, single-center, randomized controlled trial, we will investigate whether GC, with a tapering dosage, could improve organ dysfunction measured by the SOFA score in patients with aTAAD undergoing surgery.

GC is commonly used in cardiac surgery with much controversy [18]. As abundant evidence has shown that patients with aTAAD developing SIRS are more likely to suffer negative consequences, looking for novel effective treatments in this patient population to regulate such a pathophysiological process may be of paramount importance [19]. Previously, randomized controlled trials (RCTs) have emphasized on the clinical impact of intraoperative GC without considering postoperative inflammation control in cardiac surgery. Instead, in our study, sequential usage of GC will be achieved at a dosage that is widely used to treat acute severe inflammation-related conditions. Although the duration is relatively short (3 days), it fits in the clinical context and guarantees the feasibility of the study because some stable patients may leave ICU in 3 days. In addition, choosing indicators (SOFA Score) reflecting organ dysfunction increases the clinical value of the research. Data from the International Registry of Aortic Dissection has shown that organ failure is one of the leading causes of death in patients with aTAAD [1]. Examining the influence of GC with respect to the SOFA score could address this clinical quandary and potentially enhance patient survival rates.

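### Withdrawing patients for complications that need surgery, with multiple imputation as the only missing-data rule and a per-protocol set defined by complete data, can bias the primary SOFA comparison

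*Protocol article*

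**What the plan says.** Under the heading "Criteria for withdrawing from the study", the protocol article lists three grounds. The second is "Complications that require surgical treatment"; the others are glucocorticoid allergy and withdrawn consent. The heading refers to the study, not to the study drug.

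The Outcomes section makes the primary outcome the change in SOFA from POD 1, before the drug, to POD 4. It gives no value for a patient who dies before POD 4.

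The Data analysis section has three relevant rules:
- The intention-to-treat analyses are to "include all participants randomly assigned to the study arms regardless of their loss to follow-up or compliance will be implemented".
- For gaps in the data: "In case of missing data, multiple imputation will be calculated". No exception is made for death or withdrawal.
- The second analysis set is described as "Per-protocol analyses, which include all participants with complete data sets". Adherence is not part of the definition.

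The definition of postoperative infection, a secondary outcome, includes "deep incisional surgical site infection occurring at the primary chest incision" as well as mediastinitis and empyema. Such infections may need an operation.

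**The concern.** Criterion 2 is an outcome of the trial in all but name. Whether a patient meets it may depend on the allocated treatment, and a steroid's effect on infection and wound complications is a question the trial needs to answer. If meeting it ends observation, data go missing because of how the patient fared.

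The missing-data rule then applies to two quite different cases. One is a living patient whose score was not recorded. The other is a patient who died before POD 4, for whom no score exists and for whom an imputed value must be built from patients who survived. Inclusion requires only a life expectancy beyond 3 days, so deaths close to the endpoint are foreseeable.

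The per-protocol analysis gives no independent check. As defined it is a complete-case set: it loses the same patients, and it keeps any non-adherent patient whose data are complete.

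**Working it through.** **The plan's own figure.** Inputs from the Sample size section: reduction 2.87, SD 1.69, a 25% larger reduction with glucocorticoid, two-sided α = 0.10, power 0.90.

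- Planned effect: δ = 0.25 × 2.87 = 0.7175 points.
- n per arm = 2 × (1.645 + 1.282)² × 1.69² / 0.7175² ≈ 95.0, rounded up to 96; total 192. This matches.
- 192 × 1.10 = 211.2, rounded up to 212, as stated.

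So 0.72 points is the yardstick.

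**Illustration for the primary outcome.** The documents give no rates of early death or of complications needing surgery; everything in this list is assumed.

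- m = 2.87 is the mean reduction in the control patients who are observed. Observed glucocorticoid patients have m + e, with e = 0 (no effect) or e = 0.7175 (planned effect).
- pC and pG are the shares lost by POD 4 in the control and glucocorticoid arms.
- Imputation gives lost patients the mean of their own arm, so the imputed difference is e.
- The comparison scores them instead at a poor reduction w: 0 (no improvement), −2 (a rise of 2 points) or −5 (a rise of 5 points).

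Difference with poor scores = e × (1 − pG) − (pG − pC) × (m − w).

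*No true effect (e = 0; imputed difference 0):*

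| Lost, control / GC | w = 0 | w = −2 | w = −5 |
|---|---|---|---|
| 5% / 10% | −0.14 | −0.24 | −0.39 |
| 5% / 15% | −0.29 | −0.49 | −0.79 |
| 10% / 5% | +0.14 | +0.24 | +0.39 |

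For example, 0.05 × (2.87 − 0) = 0.14 and 0.10 × (2.87 + 5) = 0.79.

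*Planned effect, equal loss:* the shift is p × 0.7175, that is 0.04 at 5% and 0.07 at 10%, so the difference falls from 0.72 to 0.68 or 0.65.

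*Planned effect, unequal loss:* at 5% / 10% the difference falls to between 0.50 and 0.25. At 5% / 15% it falls to between 0.32 and −0.18. At 10% / 5% it rises to between 0.83 and 1.08.

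The 5% / 15% case averages 10% loss, which equals the plan's own dropout allowance.

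**Secondary outcomes.** A death before POD 4 is an observed event in in-hospital mortality, the composite and the log-rank test. Only deaths after withdrawal could be lost, and only if follow-up stops. Assume 8% mortality in patients not withdrawn, 5-15% withdrawn, and 20-40% mortality among those withdrawn. Imputing at 8% then misses between 106 × 0.05 × (0.20 − 0.08) = 0.6 and 106 × 0.15 × (0.40 − 0.08) = 5.1 deaths per arm of 106.

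**The case against.** The strongest reply is that the article does not say data collection ends at withdrawal. The Overview has data collected until discharge or death. The Data collection and storage section allows use of the electronic record and direct contact for additional data. The intention-to-treat sentence keeps everyone randomised. Continued follow-up is compatible with all of this. The imputation model and the handling of death are also matters that an article commonly leaves to the analysis plan, which is not shown.

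Much of that stands. Loss of later data is a plausible reading, not a stated fact, and nothing says explicitly that deaths are imputed. What remains is in the text itself: an outcome-related ground for leaving the study, an imputation rule stated without exception, and a per-protocol set defined by complete data.

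A reader might infer more than the documents support:
- *That early deaths are replaced by modelled values in the mortality comparison.* They are not; they are counted there as events.
- *That infections leading to surgery vanish from the infection outcome.* Such an infection precedes the withdrawal it triggers and can already be recorded. Only later infections are at risk.
- *That tracheotomy triggers withdrawal.* It is a named secondary outcome and part of the composite, and no text places it under criterion 2.
- *That ICU discharge removes POD 4 scores.* The remark that "some stable patients may leave ICU in 3 days" concerns stable patients, and data entry is planned through POD 4 without restriction to the ICU.
- *That the bias hides harm.* Its direction depends on which arm loses more patients.

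The illustration also assumes that imputation recovers nothing about the lost patients. A model using the earlier daily SOFA scores could close part of the gap for withdrawn patients.

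**Conclusion.** The point holds for the primary outcome, as something that should be fixed. Followed as written, the rules model or drop patients because of what happened to them after randomisation, and neither analysis set protects against this.

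The effect is small if such events are balanced between arms (0.04-0.07 points at 5-10% loss). With an imbalance of 5-10 percentage points and no true effect it is about 0.14-0.79 points, from a fifth of the planned 0.72 to slightly more than all of it. These sizes rest wholly on assumed rates and assumed poor scores, and for the primary outcome only withdrawals and deaths by POD 4 matter.

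For the secondary outcomes the risk is confined to deaths, infections and length of stay after withdrawal, and it arises only if follow-up stops then.

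**What to change.** 1. State that criterion 2 does not end study follow-up, whatever clinicians decide about treatment. Keep collecting SOFA, infection, stay and vital status to discharge for every randomised patient unless consent is withdrawn, and analyse the observed data by intention to treat.
2. Do not impute SOFA for patients who died before POD 4. Rank them worst in a Wilcoxon analysis, a test the plan already names, and limit multiple imputation to living patients with an unrecorded score.
3. Define per-protocol by receipt of the allocated regimen, with controls free of postoperative glucocorticoid, and label the present set complete-case.

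The cost is wording, follow-up of a few more patients to discharge, and a rank-based result that is less direct to interpret than a mean difference.

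Scoring deaths at the SOFA maximum of 24 and keeping the t-test would cost far more. Assume 5% deaths and a baseline SOFA of 6-12 (not in the documents). Deaths then change by +18 to +12 against −2.87 in survivors, a gap of 20.87 to 14.87. Variance = 0.95 × 1.69² + 0.05 × 0.95 × gap², so the SD rises from 1.69 to about 4.8 or 3.6, and the sample size for 0.72 points rises about 8.2-fold or 4.6-fold. Ranking avoids this.
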